## Abstract

**Methods and analysis::**

The aim of the present study is to measure muscle mass loss by measuring the thickness of the rectus femoris muscle by bedside ultrasound in critically ill patients admitted to the Intensive Care Unit (ICU) of a university hospital. Information will be collected regarding the length of hospital and ICU stay, the reason for admission, anthropometric data at admission and during hospitalization, energy needs, nutritional therapy used, and fasting time. This is a prospective, observational study that will be carried out in a single center in an ICU of a tertiary university hospital. The study population will undergo 3 tomographic images and 3 ultrasounds of the rectus femoris of each patient at different times. We propose, unprecedentedly, performing a validation study of ultrasound with the gold standard Computed tomography to evaluate the musculature of critically ill patients victims of traumatic brain injury. The results got will texto be fundamental for the development of new fields of investigation and certainly contribute to the discovery of a new approach to treat sarcopenia in critically ill patients. The Research Ethics Committee approved the study and all patients included will sign an informed consent form. (Clinical Record: RBR-2bzspnz).

## 1. Introduction

### 1.1. Background and rationale

Prolonged stays in intensive care units (ICU) are associated with sarcopenia, which is muscle atrophy associated with age and the progression of a disease.^[1]^ Its development has been related to the process of inflammation and immobilization,^[2]^ being a frequent finding in critically ill patients that may begin within the first 24 hours of admission.^[3]^ Acquired weakness in ICU patients affects 24% to 77% of patients hospitalized for over 1 week.^[4]^

The main risks for the development of muscle weakness are sepsis, mechanical ventilation, use of catecholamines, hyperglycemia, prolonged ICU stay and immobility.^[4,5]^

It is essential to use technologies for body mass assessment to identify sarcopenic patients on admission and document longitudinal changes in musculature during ICU stay.^[6]^

Body mass index (BMI) has been commonly used to identify critically ill patients at risk of malnutrition, but BMI does not distinguish between tissues such as muscle mass, fat, or edema during hospitalization^[6]^ Other markers, such as serum albumin, prealbumin, among others, do not reflect the nutritional reality of critically ill patients, since there is an increase in acute phase protein synthesis at the expense of albumin synthesis in cases of severe acute diseases^[7]^

Studies suggest that muscle wasting is an inevitable consequence in unconscious patients, and can reach 65% in 42 days in critically ill patients.^[8]^

Factors such as age, muscle function, medications, comorbidities, malnutrition, stress and muscle damage can contribute positively to the occurrence of damage and negatively to the ability to functional recovery.^[2]^ Mortality in sarcopenic patients is more than double of non-sarcopenic patients (32% vs 14%).^[9]^ There is also an association of sarcopenia with difficulty in weaning from ventilation, prolonged hospital stay, and prediction of mortality at admission within 1 year.^[3,4,6]^

It is challenging to identify patients who are at high risk for developing muscle weakness associated with ICU admission.^[10]^ Changes in muscle mass can induce dysglycemia and increase in inflammatory cytokines.^[11]^ Patients who survive ICU admission are left with sequelae and muscle weakness, and these conditions can persist for many years.^[2,3,12]^

Lower limb muscles are prone to early atrophy, shown by a greater decrease in thickness in the first few days of ICU admission compared to the upper limbs, which makes these muscles a good target for muscle mass assessment.^[12–14]^

The current techniques for assessing muscle thickness are: magnetic resonance imaging and computed tomography (CT), the latter considered the gold standard. However, these techniques have a high cost and the inconvenience of not being in the same environment as the critical patient.^[13]^ Other less expensive features, such as dual energy *X*-ray absorption, bio-impedance analysis are influenced by confounding factors such as excess fluid,^[15]^ and this situation is common in critically ill patients. Muscle measurement using ultrasound (USG), although it needs to be validated, is an easy-to-perform, accessible, safe, low-cost technique that does not use radiation and seems to be useful in the assessment of muscle mass to diagnose sarcopenia.^[2,10,12–14,16–20]^

### 1.2. Research hypothesis

The assessment of skeletal muscle mass through ultrasound agrees with the gold standard method CT.

## 2. Study objectives

### 2.1. Primary outcome

The primary endpoint will be muscle group (quadriceps) thickness. The agreement of quadriceps thickness will be verified between the images got through point-of-care ultrasound, a fast, low-cost, noninvasive method available in the ICU versus CT, the gold standard for assessing muscle thickness.

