### 2.2. Secondary outcome

The secondary outcome will include nutrition of trauma patients, associating the loss of muscle mass with caloric and protein intake and laboratory changes caused by the stress of traumatic brain injury, such as levels of creatinine, albumin, total protein fractions, protein c reactive, blood count, platelet count and bilirubin.

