## 3. Patients and methods

### 3.1. Study participants and eligibility criteria

Patients over 18 years of age, admitted to the ICU, victims of traumatic brain injury, will be included. During the acquisition of CT scans of the skull, a CT scan of the quadriceps will be performed to assess the thickness of the muscle group and compared to USG. At each CT of the control skull, at the following times: 24 hours to 96 hours and 96 hours to 168 hours after admission, controls on the thickness of the quadriceps will be performed using CT and USG and we will compare these measurements for validation of the method.

Patients with any known neuromuscular disease, such as myopathy, neuropathy or stroke, any lower limb amputated, who have undergone lower limb orthopedic surgery, or with fractures, injuries or burns in the region to be studied, pregnant women, metastatic cancer, in end-of-life care, requiring home ventilation, in prone position, transferred from another hospital after hospitalization for over 48 hours and patients in state custody. All selected patients and/or legal guardians will be advised about the study and if they agree to take part, they will sign the informed consent form (ICF).

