### 3.4. Statistical analysis

Initially, the Shapiro–Wilk test will be performed to evaluate the data distribution. Mean or median depending on the distribution of variables will describe data. To compare the values of quadriceps femoris thickness, Student’s t test or Wilcoxon test for paired samples will be applied, depending on the distribution of variables. Bland & Altman test will also be performed to assess the agreement between the methods. The relationship between caloric and protein intake, laboratory alterations and loss of muscle mass will be evaluated through multiple linear regression, with muscle mass being considered a dependent variable and caloric and protein offers and laboratory alterations being independent variables. We will use the STATA version 14 program for the analyses.

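### The aim is muscle loss, but ultrasound and CT are compared on thickness only; agreement on within-patient change is not analysed, although three paired readings would allow it

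*Protocol article*

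**What the plan says.** **Aim.** The abstract states: "The aim of the present study is to measure muscle mass loss by measuring the thickness of the rectus femoris muscle by bedside ultrasound". Section 1.1 asks for a technology that can follow musculature over the ICU stay. The Discussion presents ultrasound as a way to pick out ventilated patients who are wasting.

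**Hypothesis and primary endpoint.** Section 1.2: "The assessment of skeletal muscle mass through ultrasound agrees with the gold standard method CT". Section 2.1: "The primary endpoint will be muscle group (quadriceps) thickness", followed by "The agreement of quadriceps thickness will be verified between the images got through point-of-care ultrasound" and CT. Section 2.3 likewise describes validation of thickness measurement.

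**Data.** The abstract plans repeated pairs: "The study population will undergo 3 tomographic images and 3 ultrasounds of the rectus femoris of each patient at different times". Section 3.3.1 places the readings within 24 hours of the trauma, at 24 to 96 hours and at 96 to 168 hours after admission. They are taken by the same examiner at a marked skin point, with at most 12 hours between the techniques.

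**Method comparison.** Section 3.1 says of the readings at the control scans that "we will compare these measurements for validation of the method". Section 3.4 plans a paired t or Wilcoxon test "To compare the values of quadriceps femoris thickness", plus a Bland-Altman analysis between the methods.

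**Loss.** Section 2.2 has a secondary outcome "associating the loss of muscle mass with caloric and protein intake and laboratory changes". Section 3.4 analyses it by multiple regression. The dependent variable there is named as muscle mass, and the method that supplies it is not stated.

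**The concern.** The aim and the claimed clinical use concern change over time in one patient. The hypothesis, the primary endpoint and the stated method comparison concern thickness at a given moment. These are different questions. An offset that is stable within a patient, from probe pressure or leg position for example, spoils agreement on thickness but cancels in a change. Reading error that is independent from visit to visit enters a change score twice.

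If only thickness is compared, the study could report good agreement and have that read as evidence that ultrasound detects wasting, which was not tested. It could also report poor agreement when ultrasound follows change well. Each patient would have three thigh CT scans, and the question those repeat scans are best placed to answer would be left out of the stated analysis.

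**Working it through.** The document gives no sample size, agreement limit or margin on this point, so there is no planned figure to reproduce. The check is textual, with a short derivation and an illustration on assumed inputs.

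**1. Sections side by side**

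| Place | Quantity | Ultrasound against CT? |
|---|---|---|
| Abstract, aim | loss | no |
| 1.2 hypothesis | muscle mass | yes |
| 2.1 primary endpoint | thickness | yes |
| 3.1 control readings | thickness at each control scan | yes |
| 3.4 paired test | thickness values | yes |
| 3.4 Bland-Altman | not stated further; follows 2.1 | yes |
| 2.2 and 3.4 regression | loss (dependent variable named as muscle mass) | no |

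No row has both loss and a comparison of methods.

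**2. How the limits relate**

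Let D₁ and D₂ be the ultrasound-minus-CT differences at two visits, each with standard deviation s, and ρ their within-patient correlation.

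- Difference in change: (US₂ − US₁) − (CT₂ − CT₁) = D₂ − D₁.
- Variance: s² + s² − 2ρs² = 2s²(1 − ρ).
- Single-visit limits: mean ± 1.96·s. Change limits: mean ± 1.96·s·√(2(1 − ρ)).

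| Assumed ρ | Factor √(2(1 − ρ)) |
|---|---|
| 0 | 1.41 |
| 0.25 | 1.22 |
| 0.5 | 1.00 |
| 0.7 | 0.77 |
| 0.75 | 0.71 |
| 0.9 | 0.45 |

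The document gives no ρ. Limits for change may therefore be wider or narrower than those for thickness, and the thickness limits alone do not say which.

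**3. Illustration, all inputs assumed**

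Baseline CT thickness 2.0 cm (SD 0.5); mean CT loss 0.3 cm (SD 0.1), half of it by the second reading; ultrasound reading error SD 0.1 cm; a constant offset chosen so that the bias pooled over the three visits is zero.

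| Share of CT loss seen by ultrasound | Pooled bias, thickness | Limits, thickness | Correlation, thickness | Bias, change | Limits around that bias, change |
|---|---|---|---|---|---|
| all | 0.00 cm | ±0.20 cm | 0.98 | 0.00 cm | ±0.28 cm |
| half | 0.00 cm | ±0.24 cm | 0.97 | 0.15 cm | ±0.29 cm |
| none | 0.00 cm | ±0.33 cm | 0.95 | 0.30 cm | ±0.34 cm |

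The thickness limits do widen down the table, but nothing in them identifies missed loss as the cause.

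**4. What per-visit reporting would add**

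In the last row the bias by visit is −0.15, 0.00 and +0.15 cm. The third minus the first is 0.15 − (−0.15) = 0.30 cm, which is the bias in change. So biases reported by visit, in patients with both readings, recover the mean error in change. They do not recover the limits for individual change, because those need ρ, which two separate visit analyses do not give.

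**The case against.** **Thickness is a legitimate primary question.** Sections 1.2, 2.1, 2.3 and 3.4 are consistent with one another. This stands, and it is why change belongs as a key secondary analysis. A co-primary test would need a justified margin and would raise questions of precision. The mismatch does not rest on one abstract sentence alone, though: section 1.1 and the Discussion also argue from change and wasting.

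**Loss is analysed.** A reader might infer that the study analyses nothing but single readings. That is not so, since a regression on loss is planned. It does not compare the methods, however, so it leaves the gap open.

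**The data hold the answer.** A reader might also infer that the study is unable to say whether ultrasound tracks change. The documents do not support that: three paired readings at a marked point allow it. The gap lies in the stated analysis, not in the design.

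**Agreement may be reported by visit.** Section 3.1 allows this reading, and the document does not say that visits are pooled. A systematic failure to follow mean loss would then show. The illustration above pools visits and sets the offset to force a zero bias, so it shows what is possible, not what is likely. The limits for individual change would still be missing.

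**This is a condensed article.** An unseen full protocol or analysis plan may contain a change analysis, and its absence there cannot be asserted. But the article itself fixes the endpoint and comparison on thickness while its aim and claimed use are loss. That mismatch is in the text shown.

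**Conclusion.** The point holds in a limited form. The stated ultrasound-versus-CT comparison concerns thickness, the planned analysis of loss does not compare methods, and so the analysis as described will not show whether ultrasound tracks individual change as CT does. Thickness agreement cannot substitute: the factor between the two sets of limits runs from 1.41 at ρ = 0 to 0.77 at ρ = 0.7 and 0.45 at ρ = 0.9. This assumes an equal SD of differences at both visits, and every ρ is an assumption.

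A reader might go further, scale section 1.1's upper figure of 65% wasting in 42 days to a week (65 × 7/42 = 10.8%), and judge whether ultrasound could resolve such a loss in one patient. The documents do not support that step:

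- They give no limit of agreement and no ρ to set against the loss.
- The 65% is an upper figure for muscle wasting, not for quadriceps thickness.
- The third reading may fall at 96 hours, where the same linear scaling gives 65 × 4/42 = 6.2%.
- Resolving a loss by ultrasound in one patient depends on ultrasound's own repeatability, whereas the SD of ultrasound minus CT also contains CT error.

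The size of the problem is therefore the undetermined factor above, not a demonstrated failure to detect loss.

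**What to change.** Add to section 3.4, as a key secondary analysis, the Bland-Altman bias and limits of agreement, each with a 95% confidence interval, for the within-patient change by ultrasound against CT: reading 2 minus reading 1, and reading 3 minus reading 1. Each contrast gives one value per patient.

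State that any claim about detecting muscle loss rests on this analysis, and any claim about absolute thickness on the thickness analysis.

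The cost is one extra analysis on data already planned, with no further scans. It is restricted to patients who have both paired readings for the contrast, so the number contributing to each should be reported.

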### 2.2. Secondary outcome

The secondary outcome will include nutrition of trauma patients, associating the loss of muscle mass with caloric and protein intake and laboratory changes caused by the stress of traumatic brain injury, such as levels of creatinine, albumin, total protein fractions, protein c reactive, blood count, platelet count and bilirubin.

### 2.3. Design

Prospective, observational study to validate the use of US to measure muscle thickness in ICU patients. The research will be carried out in an ICU of a tertiary university hospital.

## 3. Patients and methods

### 3.1. Study participants and eligibility criteria

Patients over 18 years of age, admitted to the ICU, victims of traumatic brain injury, will be included. During the acquisition of CT scans of the skull, a CT scan of the quadriceps will be performed to assess the thickness of the muscle group and compared to USG. At each CT of the control skull, at the following times: 24 hours to 96 hours and 96 hours to 168 hours after admission, controls on the thickness of the quadriceps will be performed using CT and USG and we will compare these measurements for validation of the method.

Patients with any known neuromuscular disease, such as myopathy, neuropathy or stroke, any lower limb amputated, who have undergone lower limb orthopedic surgery, or with fractures, injuries or burns in the region to be studied, pregnant women, metastatic cancer, in end-of-life care, requiring home ventilation, in prone position, transferred from another hospital after hospitalization for over 48 hours and patients in state custody. All selected patients and/or legal guardians will be advised about the study and if they agree to take part, they will sign the informed consent form (ICF).

### 3.2. Randomization and allocation

There will be no randomization, as all patients will undergo the exams. After the study team confirms that a subject meets all the study entry criteria, they will be included and all patients will receive a copy of the informed consent form to take part in the study, besides the verbal explanation of the step-by-step of the study.

### 3.3. Study procedures

#### 3.3..1.
*Study protocol*.

Anthropometric, clinical and nutritional data will be collected: height, weight, BMI, injury severity score,^[21]^ prognostic scores SAPS-3^[22,23]^ and APACHE II,^[24]^ number of days of mechanical ventilation and ICU and hospital stay,^[3]^ NUTRIC score,^[25]^ NRS 2002^[26]^ and basal energy expenditure through pocket formula with calorie and protein requirements.

Weight will be measured on a Stryker scale stretcher, height will be used standard body tape measure, measurements will be taken at the time of admission of the patient to the ICU. BMI will be classified according to the World Health Organization 1995.^[27]^

Daily, the volume of diet and protein intake will be recorded until the seventh day of hospitalization, and the percentage of diet intake will then be calculated by the ratio of the amount actually ingested to the amount prescribed.

The USG will be performed with a Sono Site M-Turbo device with 2-dimensional mode, with a linear transducer (frequency: 7–13MHz) to get high-resolution images of surface structures 1, in cross-section, in B-mode, with the transducer oriented transversely to the longitudinal axis (the imaginary line marked before) of the thigh forming a 90° angle in relation to the skin surface with minimal pressure on the skin (Fig. 1).

**Figure 1. F1:**
[figure not shown]
Illustrative photo to characterize the gained images (CT and USG). CT = computed tomography, USG = ultrasonography.

The measurement will be performed with the patient in a supine position with the leg extended and relaxed, at the midpoint between the anterosuperior iliac spine and the proximal edge of the patella, where the quadriceps femoris will be visualized, a muscle group in the thigh, formed by 4 muscles: vastus medialis, intermedius, lateral and rectus femoris.^[15]^ Subsequently, we will use planimetric techniques to measure distances and areas: Thickness: from the muscle-fat interface to the muscle-muscle interface or from the muscle-fat interface to the bone surface,^[8]^ forming a straight horizontal line and; manually describing the thickness of the quadriceps femoris.

Measurements will be got at the time of admission of the patient to the hospital, preferably still in the trauma room, within 24 hours of the trauma. Second measurement 24 hours to 96 hours after admission, preferably in the ICU and third measurement 96 hours to 168 hours after admission. All USG measurements will be performed simultaneously with quadriceps CT, with a maximum interval of 12 hours between 1 technique and another. The study protocol is represented in Figure 2.

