**Figure 2. F2:**
[figure not shown]
Compendium of study design.

Measurements will be got by 2 operators, intensive care physicians, trained in using bedside USG in the ICU. The standardization of USG measurements was previously published, whose correlation analysis found an excellent interobserver relationship (*R*2 > 0.90)^[28]^

Care will be taken during the handling of patients so that all measurements do not entail greater risks for them, except for the discomfort caused by the exam. The same examiner will make all measurements and, at the same point, as we will mark the studied limb with a marker pen and cover with plastic film.

We will perform the tomographic control exams of the thigh only in the studied region through the marking performed, to reduce: radiation dose to patients, costs and exam time. The CT analyzes will be interpreted by a radiologist and we will have 3 images per patient.

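### Follow-up scan windows are 72 hours wide but the muscle-loss regression has no term for elapsed time, and the 48-hour transfer rule conflicts with the 24-hour baseline rule

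*Protocol article*

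**What the plan says.** **Timing.** Section 3.3 places the first scan at hospital admission, "preferably still in the trauma room, within 24 hours of the trauma". The later scans are set as "Second measurement 24 hours to 96 hours after admission, preferably in the ICU and third measurement 96 hours to 168 hours after admission". The text does not say whether admission here means to the hospital or to the ICU, and neither window has a target time.

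**Pairing.** Also in section 3.3: "All USG measurements will be performed simultaneously with quadriceps CT, with a maximum interval of 12 hours between 1 technique and another".

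**Eligibility.** The list in section 3.1 that can only be read as exclusions includes patients "transferred from another hospital after hospitalization for over 48 hours".

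**Trigger and number of scans.** Section 3.1 attaches the follow-up thigh measurements to the control head scan: "At each CT of the control skull, at the following times: 24 hours to 96 hours and 96 hours to 168 hours after admission". Section 3.3 says of the CT readings: "The CT analyzes will be interpreted by a radiologist and we will have 3 images per patient". The abstract likewise plans three CT images and three ultrasounds per patient.

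**Analysis.** Section 3.4 relates muscle loss to intake and laboratory changes by multiple linear regression. Muscle mass is the dependent variable, and calorie supply, protein supply and laboratory changes are the independent variables. Scan time is not among them. Muscle loss is the aim stated in the abstract and belongs to the secondary outcome (section 2.2). The primary outcome (section 2.1) is agreement between ultrasound and CT.

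**The concern.** Muscle loss accumulates with time, so a loss figure has meaning only together with the interval over which it was measured. Under this schedule, one patient's second scan may come one day after admission and another's four days after. The regression as described treats the two losses as the same quantity.

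If scan timing is unrelated to intake and laboratory values, the result is extra noise and lower precision. If it is related, for example because the clinical course influences when scans take place, the coefficients for intake and laboratory values absorb part of the effect of time. The article does not show which of these applies.

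The eligibility rule raises a second difficulty. Some patients can enter the study although their first scan cannot meet the baseline rule, and the article does not say what happens to them in the loss analysis.

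**Working it through.** The article gives no figure of its own on this point to reproduce. The check is interval arithmetic on the stated windows, followed by an illustration using the wasting rate that the article cites.

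**Inputs**
- Scan 2 window: 24 to 96 h after admission (sections 3.1 and 3.3).
- Scan 3 window: 96 to 168 h after admission (same sections).
- Baseline: at admission and within 24 h of trauma (section 3.3).
- Wasting rate: up to 65% in 42 days (section 1.1), an upper figure.

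**Step 1: width of the windows**
- Scan 2: 96 − 24 = 72 h.
- Scan 3: 168 − 96 = 72 h.
- Scan 2 to scan 3: from 96 − 96 = 0 h to 168 − 24 = 144 h.

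**Step 2: interval from a baseline at admission**
- To scan 2: 24 to 96 h, ratio 96/24 = 4.
- To scan 3: 96 to 168 h, ratio 168/96 = 1.75.

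If the baseline scan may fall anywhere from 0 to 24 h after admission (an assumption), the intervals become 0 to 96 h and 72 to 168 h. If admission itself follows trauma by 0 to 24 h (also an assumption), scan 2 falls 24 to 120 h and scan 3 falls 96 to 192 h after trauma.

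**Step 3: what timing alone does to apparent loss**

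Linear: 65/42 = 1.548 percentage points per day. Exponential: rate = −ln(0.35)/42 per day, loss = 1 − exp(−rate × days).

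| Hours from baseline | Linear loss | Exponential loss |
|---|---|---|
| 24 | 1.5% | 2.5% |
| 96 | 6.2% | 9.5% |
| 168 | 10.8% | 16.1% |

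Two patients wasting at the same rate could therefore show 1.5% and 6.2% at scan 2, or 6.2% and 10.8% at scan 3 (linear).

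**Step 4: a less extreme summary**

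The figures above are the ends of the windows. If scan times were spread evenly over each window (an assumption), their standard deviation would be 3/√12 = 0.87 day. That is 0.87/2.5 = 35% of the mean interval to scan 2 and 0.87/5.5 = 16% of the mean interval to scan 3.

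**Step 5: transfer rule against baseline rule**

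A stay in another hospital follows the trauma. A patient who arrives after more than 24 h and up to 48 h elsewhere is not excluded by section 3.1, but is already beyond the 24 h from trauma that section 3.3 allows for the first scan. Both rules cannot hold for this patient.

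**Step 6: trigger against number of images**

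Section 3.1 performs follow-up scans when a control skull CT is done. Section 3.3 and the abstract count three per patient. The two agree only if every patient has a control skull CT in each window, which the article does not state.

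**The case against.** **The article is a summary, and a fuller analysis plan may include time.** This is fair as far as it goes. But section 3.4 does not leave the model open: it names the dependent variable and the kinds of independent variable. The point is about the model as described, and it falls away if an unseen plan already includes elapsed time.

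**The ratios only restate the windows, and 65% in 42 days is an extreme.** Correct. The 4-fold and 1.75-fold ratios are 96/24 and 168/96, and the percentages are endpoints at an upper rate. They show how much room the schedule leaves for timing and do not estimate a bias. The distribution of scan times is unknown.

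**Wide windows are a pragmatic choice.** This stands, and the windows need not be narrowed if time is recorded and modelled.

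A reader might also infer several stronger points that the article does not support:
- *That the primary result is compromised.* Ultrasound and CT are compared within a time point, at most 12 h apart, so window width does not bias the paired difference.
- *That baseline and follow-up have plainly different time zeros.* Baseline is also set at admission, with an added cap measured from trauma. The anchors are mixed and incompletely defined, but admission is common to both.
- *That the loss sample over-represents patients who still need imaging.* This requires control skull CT to be done on clinical indication. The article does not say so, and it promises three images per patient.
- *That late transfers will have an already reduced baseline.* This happens only if the 24 h rule is broken. What the text shows is a conflict between two rules.
- *That simultaneous scanning contradicts the 12 h allowance.* The same sentence states the allowance as its tolerance.

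**Conclusion.** The concern holds for the muscle-loss analysis. As written, the regression treats measurement intervals that differ up to 4-fold (scan 2) or 1.75-fold (scan 3) as equivalent. These ratios assume a baseline at admission. The 1.5% to 6.2% and 6.2% to 10.8% ranges further assume constant loss at the article's upper rate and are illustrative only. Whether the consequence is mainly noise or also confounding cannot be settled from the article.

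The conflict between the 48 h transfer exclusion and the 24 h baseline rule is a real inconsistency in the text. Its size cannot be given, because the article does not state how many transfers are expected. The link between follow-up scans and control skull CT also needs to be reconciled with the promised three images per patient. Any selection effect from that link remains conditional.

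The correction should be made, because loss is the abstract's stated aim and part of the secondary outcome, and scan times that were not recorded may be impossible to recover later.

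**What to change.** 1. Define one time zero for all scans, and say whether admission means to the hospital or to the ICU.
2. Record the exact date and time of every ultrasound and CT.
3. Add actual elapsed hours between baseline and follow-up scan as a covariate in the loss regression already planned in section 3.4. Loss per day is a simpler alternative, but it assumes a constant rate, and section 4 cites work in which the largest losses came in the first days.
4. Reconcile the transfer exclusion with the 24 h baseline rule, or restrict the loss analysis (not the agreement analysis) to patients whose first scan is within 24 h of trauma.
5. Reconcile section 3.1 with the promise of three images per patient by stating that the bedside ultrasound already planned for each window is done even if no control skull CT takes place. Such an ultrasound serves the loss analysis only, since it has no CT to be paired with.

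**Cost.** One extra model term, time stamps and some rewording. A few late transfers may leave the loss analysis. No ultrasound is added beyond the three already planned per patient, and the primary agreement analysis is unchanged.

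### The secondary muscle-loss regression names no time variable, although the last scan may fall anywhere from about 4 to 7 days after admission

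*Protocol article*

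**What the plan says.** Section 3.3 (text after Figure 1) places the first measurement at hospital admission, "preferably still in the trauma room, within 24 hours of the trauma". It then gives the follow-up times: "Second measurement 24 hours to 96 hours after admission, preferably in the ICU and third measurement 96 hours to 168 hours after admission". Section 3.1 says what fixes the hour inside each window, namely the repeat head scan: "At each CT of the control skull, at the following times: 24 hours to 96 hours and 96 hours to 168 hours after admission". No study hour is set within either 72-hour window.

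Section 2.2 makes the association of muscle loss with intake and laboratory changes the secondary outcome. Section 3.4 gives the method: "The relationship between caloric and protein intake, laboratory alterations and loss of muscle mass will be evaluated through multiple linear regression". The same sentence names muscle mass as the dependent variable, and caloric and protein offers and laboratory alterations as the independent variables. Time since the first scan is not among them. Section 3.4 does not state which pair of scans defines loss or whether loss is scaled.

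Section 3.3 also has diet and protein intake recorded daily to the seventh hospital day for every patient, whatever the date of the last scan.

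**The concern.** Muscle loss accumulates with time. If patients are observed for unequal times and the model has no time term, two patients wasting at the same daily rate receive different outcome values because their scans fell on different days.

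At the least this adds noise and weakens the secondary analysis. It becomes bias if a predictor also moves with scan time. That could happen if laboratory values change with time since injury, or if the hour of the control skull CT follows clinical severity, which may also influence feeding and laboratory results. A timing effect could then be reported as a nutritional or laboratory association.

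This goes beyond detail that an article leaves to a fuller plan, because section 3.4 does list the model's variables and time is not one of them.

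**Working it through.** The article states no figure for this analysis, so there is nothing to reproduce. The check has four steps.

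**1. Elapsed time, from the windows in section 3.3**
- First scan at admission (0 h), third scan at 96 to 168 h: 96/24 = 4 days to 168/24 = 7 days; ratio 168/96 = 1.75.
- If the first scan were delayed a full 24 h after admission and the third taken as early as allowed: 96 − 24 = 72 h, or 3 days.
- If loss were instead taken from admission to the second scan: 24 to 96 h, a ratio of 4.

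**2. Effect of timing on expected loss**

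The only loss-over-time figure is in section 1.1, where wasting "can reach 65% in 42 days in critically ill patients". Taken as a constant daily rate for illustration: 65/42 = 1.548 percentage points per day.
- Day 4: 4 × 1.548 = 6.2%
- Day 7: 7 × 1.548 = 10.8%

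With an exponential decline the daily loss is 1 − 0.35^(1/42) = 2.47%, giving 9.5% at day 4 and 16.1% at day 7.

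**3. Share of the variance of loss due to timing**

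Assumptions, not in the article: third scan uniform over 4 to 7 days; mean rate 1.548 points/day; between-patient rate SD s of 0.3 to 0.8 points/day, independent of timing; measurement SD of 0 or 2 points.
- Timing variance: (1.548 × 3/√12)² = (1.548 × 0.866)² = 1.80
- Rate variance: s² × (5.5² + 0.75) = 31 s²
- Share = 1.80 / (1.80 + 31 s² + measurement variance)

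| s (points/day) | 31 s² | Share, no measurement error | Share, measurement SD 2 |
|---|---|---|---|
| 0.3 | 2.79 | 39% | 21% |
| 0.5 | 7.75 | 19% | 13% |
| 0.8 | 19.84 | 8% | 7% |

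**4. False-positive rate for an intake effect that is truly zero**

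Simulated ordinary least squares with n = 60 (assumed), scans over 4 to 7 days, rate SD 0.5, measurement SD 2, nominal level 5%.
- Intake unrelated to scan time: about 5%, which is noise and not bias.
- Linear loss, timing-severity correlation 0.2, intake wholly determined by severity: about 8%.
- Linear loss, timing-severity correlation 0.5, intake correlated about 0.7 with severity: 15% to 16%. A closer link between intake and severity raises it further.
- The same 0.5 and 0.7 correlations, but loss concentrated early (assumed time constant 3 days): about 7% for unscaled loss, 10% to 11% for loss per day, and 5% with elapsed time as a covariate.

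The time covariate kept the rate near 5% in every scenario. Loss per day did so only when loss was linear.

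**The case against.** **The span is narrower than it first looks.** A reader might infer a 3-to-7-day span and a more than twofold difference. The text does not support that as the ordinary case. The first scan is set at admission, and its limit ("within 24 hours of the trauma") runs from the injury, while the follow-up windows run from admission. Subtracting one clock from the other gives 72 h only if admission coincides with the injury and the first scan is then delayed by nearly a day. This objection stands: the working figure is 4 to 7 days.

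**Intake is not tied to the scan date.** A reader might infer that intake builds up to the scan, so that intake and loss grow together and false positives become frequent. Section 3.3 records intake to day 7 for everyone and takes it as a ratio of ingested to prescribed. Nothing says that it is cumulated or averaged to the last scan, so rates simulated on that basis do not describe this plan. This also stands.

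**Bias is conditional.** Section 3.1 links the scans to control skull CTs but does not say that severity sets the hour within a window. That link is an inference. Without it, or some other link between exposures and timing, the cost is lost precision only.

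**The rate is an upper figure.** The 65% is what wasting can reach, not an average, and a lower mean rate shrinks every timing effect above.

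**The text is condensed.** Section 3.4 does not define loss or the unit of analysis, and a fuller plan may scale it. That limits how firmly one can say what will be done. It does not remove the point, because the predictors are listed and time is absent.

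**Conclusion.** The point holds for the secondary regression only. As written, the model compares losses accrued over about 4 to 7 days (ratio up to 1.75) without accounting for the interval. At the article's upper rate, taken as linear, timing alone moves loss from 6.2% to 10.8%. With assumed rate SDs of 0.3 to 0.8 points/day, timing accounts for 39% to 8% of the variance of loss without measurement error, and 21% to 7% with a measurement SD of 2 points.

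Whether this biases the nutrition and laboratory coefficients cannot be settled from the article. The false-positive rate is about 5% if exposures are unrelated to timing, and about 16% under linear loss with n = 60 and a timing-severity correlation of 0.5. Sample size, spread and correlations are all assumptions. The documents do not support the claim that the regression will mainly measure scan timing.

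The primary ultrasound-CT comparison is untouched, because section 3.3 keeps each pair of scans within 12 hours.

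**What to change.** In section 3.4, add the actual hours from the first scan to the follow-up scan as a covariate, taken from the image time stamps, and state which scan pair defines loss.

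Preferably, fit a mixed model of thickness at all three scans on actual time. It should allow for non-linear loss, and intake and laboratory values should interact with time so that they act on the course of loss.

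Do not rely on simple percent loss per day. It assumes constant loss, whereas section 4 cites a sepsis study in which the largest losses came in the first days. Under that pattern, patients scanned earlier get higher per-day values, and the distortion can exceed that of unscaled loss.

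The cost is one more model term, or a slightly more complex model. No scan, visit or procedure changes. Section 3.5 says data come directly from the ultrasound and CT devices, so acquisition times should be recoverable.
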